## Abstract

**Background:**

Digital health interventions (DHIs) can alleviate several barriers to achieving better maternal and child health. The World Health Organization’s guideline recommendations for DHIs emphasize the need to integrate multiple DHIs for maximizing impact. The complex health system of Bangladesh provides a unique setting for evaluating and understanding the role of an electronic registry (eRegistry) for antenatal care, with multiple integrated DHIs for strengthening the health system as well as improving the quality and utilization of the public health care system.

**Objective:**

The aim of this study is to assess the effect of an eRegistry with DHIs compared with a simple digital data entry tool without DHIs in the community and frontline health facilities.

**Methods:**

The eRegMat is a cluster-randomized controlled trial conducted in the Matlab North and Matlab South subdistricts in the Chandpur district, Bangladesh, where health facilities are currently using the eRegistry for digital tracking of the health status of pregnant women longitudinally. The intervention arm received 3 superimposed data-driven DHIs: health worker clinical decision support, health worker feedback dashboards with action items, and targeted client communication to pregnant women. The primary outcomes are appropriate screening as well as management of hypertension during pregnancy and timely antenatal care attendance. The secondary outcomes include morbidity and mortality in the perinatal period as well as timely first antenatal care visit; successful referrals for anemia, diabetes, or hypertension during pregnancy; and facility delivery.

**Results:**

The eRegistry and DHIs were co-designed with end users between 2016 and 2018. The eRegistry was implemented in the study area in July 2018. Recruitment for the trial started in October 2018 and ended in June 2020, followed by an 8-month follow-up period to capture outcome data until February 2021. Trial results will be available for publication in June 2021.

**Conclusions:**

This trial allows the simultaneous assessment of multiple integrated DHIs for strengthening the health system and aims to provide evidence for its implementation. The study design and outcomes are geared toward informing the living review process of the guidelines for implementing DHIs.

**Trial Registration:**

ISRCTN Registry ISRCTN69491836; https://www.isrctn.com/ISRCTN69491836

**International Registered Report Identifier (IRRID):**

DERR1-10.2196/26918

## Introduction

### Background

The evidence-based interventions that can prevent maternal, newborn, and fetal deaths are well known [1], but the lack of access to timely and actionable data is a significant obstacle toward achieving better maternal and child health [2]. Much of the existing data for monitoring maternal and child health in low- and middle-income countries (LMICs) come from national surveys, such as the Demographic and Health Surveys [3] and the Multiple Indicator Cluster Surveys [4]. Health information systems in LMICs, which can provide routine and critical data, are often underutilized. In many settings, health information systems do not collect and manage data in ways that provide personalized good quality health care [5]. Other known issues such as the lack of awareness of guidelines, inadequate feedback to providers, and a poor coordination between the levels of health care have been shown to hamper effective data use [6].

Digital health interventions (DHIs) have the potential to address many of these issues. In 2017, the World Health Organization (WHO) published the Classification of DHIs, describing how digital tools can support health and health systems [7], whereas in 2019, their first recommendations for a select set of DHIs for health system strengthening were released [8]. Even for the DHIs included in the WHO guidelines, there is insufficient evidence to fully inform their optimal implementation in health systems. Evidence for the use of DHIs at a large scale in the real-world settings is crucial for policy makers to make decisions about system-wide implementations [9]. Every recent review of DHIs has unequivocally stated the need for more evidence of what works, and if and how such DHIs can be made scalable and sustainable [10,11]. DHIs are frequently tested in isolation or with weak study designs [8], making it difficult to ascertain their efficacy. The combinations of DHIs may be most effective in delivering measurable impacts on strengthening the health system. Many countries have transitioned to the use of digital health information systems. The enormous amount of data collected in such systems can be harnessed to drive several DHIs to strengthen the health systems, an opportunity often missed. Although evaluations of digital health information systems have focused on assessing timeliness and completeness of routine data, more comprehensive assessments of the outcomes of implementations of DHIs driven by data collected in health facilities are relatively rare.

An electronic registry (eRegistry) is a digital health information system comprising the longitudinal tracking of clients’ health status and services received, typically for maternal and child health [12]. In a health system with an eRegistry, health workers enter clinical data at the point of care into digital client health records. Data entry is typically set up as interactive checklists, which can minimize the documentation burden while enhancing data quality. The entered clinical data then drives several DHIs, for example, guideline-based clinical decision support for health workers [13] and targeted communication of personalized health information to clients [14]. An eRegistry can support additional DHIs such as feedback dashboards, stock notifications, routine health indicator data collection and management, and referral management. The specific set of DHIs included in an eRegistry, beyond the longitudinal tracking of clients’ health status, depends on the exact needs of a given implementation context.

Since 2018, an eRegistry has been implemented for use in Bangladesh in the Matlab North and Matlab South Upazilas, Chandpur district. Bangladesh has made significant progress in terms of maternal and child health. From 1990 to 2013, the Millennium Development Goal 4 was achieved (reduction of under-five mortality from 133 to 52 per 1000 live births), whereas maternal mortality declined significantly (from 550 to 196 per 100,000 live births) [15]. The primary health care system, where a large portion of maternal and child health services are provided, is a complex landscape of governmental, private, and nongovernmental organization (NGO) providers. The digital health atlas, an open-source platform for DHI implementations maintained by WHO, lists at least 12 registered implementations of DHIs in Bangladesh as of September 2020 [16].

The first cluster-randomized controlled trial of the effectiveness of an eRegistry with clinical decision support compared with paper records on improving the quality of antenatal care was conducted in the West Bank, Palestine [13]. The effect of an eRegistry with multiple DHIs such as health worker clinical decision support, feedback dashboards with action items, and targeted client communication, compared with a simple digital data entry tool with no DHIs, is yet to be evaluated.

### Objectives

The objective of this eRegistry trial (eRegMat) in Matlab, Bangladesh, is to assess the effect of an eRegistry with DHIs compared with a simple digital data entry tool without any DHIs in the community and frontline health facilities.

## Methods

### Trial Design

The eRegMat study is a two-arm cluster-randomized controlled trial. The unit of randomization is the primary care health facility, community clinics, and family welfare clinics. All pregnant women enrolled in the trial had their health information entered into the eRegistry. The intervention arm received 3 DHIs supported by the data in the eRegistry: (1) health worker clinical decision support, (2) feedback dashboards with action items, and (3) targeted client communication. The control arm received only a digital data entry tool without any additional DHIs.

### Study Setting

The public health system in two Upazilas (subdistricts)—Matlab South and Matlab North under Chandpur, Bangladesh—were included in the eRegMat trial. The public health system in Bangladesh is managed by the Ministry of Health and Family Welfare, where maternal and child health services are provided by two separate departments: the Directorate General of Family Planning and the Directorate General of Health Services. Under the Directorate General of Family Planning, family welfare visitors work at family welfare clinics located at the union level and family welfare assistants provide community outreach services. Under the Directorate General of Health Services, community health care providers offer maternal and child health as well as general health services from community clinics and health assistants who are tasked with visiting households and providing vaccination services to women and girls of reproductive age as well as young children through satellite clinics set up close to the community. A typical primary care health facility (community clinic or family welfare clinic) is permanently staffed by one clinical cadre (a community health care provider or a family welfare visitor). In addition, at the community clinics, the community health care provider is usually supported by a family welfare assistant or a health assistant. The community and facility workers cooperate to register pregnancies and encourage clients to seek reproductive, maternal, and child health services. In the existing paper-based health information system environment, there is no exchange of data or information between the different cadres of health workers or the different levels of the health system. The District Health Information Software 2 (DHIS2) [17] was used to generate aggregate reports of maternal and child health contacts in the study area.

In the study area, a substantial number of pregnant women access care at family welfare clinics and community clinics within the governmental health system. Antenatal care typically comprises the measurement of blood pressure, height, weight, fundal height; anemia assessment; the provision of vitamin and mineral supplementation; management of common illnesses; counseling; and referral, if needed. On the basis of these guidelines, pregnant women with complications are referred to a subdistrict (Upazila) hospital, where basic laboratory services as well as delivery services including cesarean sections are typically available. Some patients utilize tertiary care health facilities for delivery or when identified with complications during pregnancy. Women may also access private health care, where they are likely to receive ultrasound scans and laboratory tests. Most private hospitals perform cesarean sections. Several private and NGO-run facilities are also engaged in providing maternal and child health services in the study area.

### Eligibility Criteria

There were 2 levels of eligibility for this trial: (1) the cluster level, which refers to the randomized health facilities and their health workers and (2) the individual level, which refers to the women belonging to the clusters who provide informed consent.

#### Cluster Level

All government-run community clinics and family welfare clinics routinely providing antenatal care, delivery, or postnatal care services outside the referral health facility in the Matlab North and Matlab South Upazilas were eligible for the trial. Facilities were excluded if (1) there was no community health care provider or family welfare visitor to provide information on antenatal care visits in the previous month or (2) they reported fewer than five antenatal care visits in the previous month. Of the 72 health facilities in the study area, 59 (82%) were randomized (Figure 1). In total, 30 health facilities and 59 health workers were allocated to the intervention arm, whereas 29 health facilities and 64 health workers were allocated to the control arm (Figure 1).

**Figure 1 figure1:**
[figure not shown]
Flow diagram. eRegistry: electronic registry.

#### Individual Level

Individual women with a confirmed pregnancy were registered, and their health data were entered into the eRegistry. Pregnancy identification and registration may be conducted by family welfare assistants or health assistants at the households or by community health care providers or family welfare visitors at the women’s first health facility encounter. All pregnancies identified by a health worker using the eRegistry should be entered into the system. Only women who consent to have a household visit after birth were included in the trial because the outcome data were derived from the household survey.

### Intervention

#### Overview

An eRegistry was implemented in the study area by the International Centre for Diarrhoeal Disease Research, Bangladesh (icddr, b), in collaboration with the Norwegian Institute of Public Health, the University of Oslo, and the Ministry of Health and Family Welfare in Bangladesh. Health workers in both the intervention and control arms document clinical information in the eRegistry’s digital client health records at the point of care. Health workers’ cadres under both the Directorate General of Health Services and Directorate General of Family Planning (Table 1) use the eRegistry to create client health records across otherwise disjointed silos of the health information system. The eRegistry is configured in the free and open-source DHIS2 tracker. Health workers in the community (family welfare assistants and health assistants) use the eRegistry on a customized Android Tracker app installed on handheld tablets, whereas facility-based users (community health care providers and family welfare visitors) access the eRegistry through a browser on Chromebook (Figure 2). All devices were equipped with SIM cards for prepaid mobile data access. To improve client identification for optimal data continuity in an environment with a few unique identifiers, a palm-based biometric software provided by Element biometrics [18] was made available to the users of the eRegistry. The Element biometrics app was installed on the same device used by the health workers to access the eRegistry. A unique identifier was generated for each client in the biometrics app. Health workers were trained to copy this identifier to the client’s records in the eRegistry. A unique identifier was also generated by the DHIS2 system during the registration of each pregnancy. A demo version of the eRegistry and DHIs is available upon request from the authors.

Paper-based documentation of pregnancies; register books with the number and dates of antenatal, postnatal, and delivery services; and public health reports were maintained along with the eRegistry in both intervention and control health facilities throughout the trial period. Table 1 provides a detailed comparison of the situation before eRegistry implementation in the governmental health system with the control and intervention arms of the trial.

**Table 1 table1:** The paper-based health information system before the implementation of electronic registry, the electronic registry in the control arm, and the electronic registry with digital health interventions in the intervention arm.

Health information system feature		Cadres	Before the trial	Control arm	Intervention arm
**Health worker: all**					
	Access to own records	FWA^a^, HA^b^, CHCP^c^, FWV^d^	✓^e^	✓	✓
	Access to all records in the system	CHCP, FWV			✓
**Health worker: community**					
	Digital client health records	FWA, HA		✓	✓
	Client identification (biometric and palm-based) and registration	FWA, HA		✓	✓
	Feedback dashboards	FWA, HA			✓
**Health worker: facility**					
	Client identification (biometric and palm-based) and registration	CHCP^f^, FWV		✓	✓
	Digital client health records	CHCP^f^, FWV			✓
	Clinical decision support	CHCP^f^, FWV			✓
	Feedback dashboards	CHCP^f^, FWV			✓
**Health worker: all**					
	Access to own records	FWA, HA, CHCP, FWV	✓	✓	✓
	Access to all records in the system	CHCP, FWV			✓
**Clients**					
	Targeted Client Communication via SMS	Pregnant women			✓

^a^FWA: family welfare assistant.

^b^HA: health assistant.

^c^CHCP: community health care provider.

^d^FWV: family welfare visitor.

^e^Features of the eRegistry with and without digital health intervention available in the intervention and control arms.

^f^Community health care providers use the District Health Information Software 2 system for separate aggregate reporting, not linked to the electronic registry.

**Figure 2 figure2:**
[figure not shown]
Screenshot of electronic registry interface for data entry in the study area—intervention and control clusters.

#### Control Arm

In the control arm of the trial, the eRegistry comprised only digital client health records (Table 1). The data points included in the client records were almost identical to the paper-based client records, and drop-down lists were added to some data points to optimize the use of the digital data entry tool. The eRegistry in the control arm was set up such that control users had no access to client records entered by other users. Apart from basic data validation warnings, data-driven DHIs were not available in the control arm (Table 1).

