#### Intervention Arm

In the intervention arm, the eRegistry supported 3 data-driven DHIs linked to the digital client health records (Table 1) as follows: (1) for facility-based staff, health worker clinical decision support based on national guidelines to promote the correct management of health conditions identified in antenatal care; (2) for both field- and facility-based staff, feedback dashboards tracking the health worker’s progress toward pregnancy registration, antenatal care attendance and utilization, and clinical screening and management targets; and (3) for pregnant women, targeted client communication in the form of SMS text messages to address gaps in the timely attendance of antenatal care visits and facility delivery. Following the initial implementation of the eRegistry, the DHIs in the intervention arm were gradually introduced over the course of the trial; health worker clinical decision support was introduced in October 2018; targeted client communication via SMS and feedback dashboards were implemented in June 2019. Digital client health records were accessible across the cadres of health workers, facilities, and arms of the health system for a comprehensive longitudinal tracking of clients’ health status and services received (Table 1).

Guideline-based clinical decision support and feedback dashboards were developed in close collaboration with health workers. The decision support comprised referral and counseling reminders, medication alerts, and scheduling based on the recommended guidelines in the public health system. Feedback dashboards were customized for each cadre of health workers, with indicators of antenatal care attendance and screening and management of gestational diabetes, hypertension, and anemia. Targeted client communication included SMS text message reminders of routine antenatal care, referral facilitation SMS text messages for those at risk, and facility delivery reminders for those who are advised to have an institutional delivery. All DHIs were triggered by data entry into the eRegistry at the point of care by the health workers.

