### Outcomes

The outcomes were formulated based on their relevance to the health system context and were meant to capture the potential effects of the specific DHIs under assessment. Data for the primary (Table 2) and secondary outcomes (Table 3) will be derived from the eRegistry’s client health records and through postpartum home visit interviews.

**Table 2 table2:** Primary outcomes, data sources, and definitions.

Primary outcome	Sources of data	Measurement sequence	Definition	Intervention subcomponents with most direct effect
Timely attendance at eligible ANC^a^ visits	Postpartum household survey	Registrations continuously at point of care Household visit after the completion of pregnancy	Proportion with timely attendance	Targeted Client Communication via SMS text message: ANC appointment reminders
Screening and management for hypertension in pregnancy	Case records from the eRegistry^b^	Registrations continuously at point of care	Proportion that has at least one ANC at a randomized health facility with: Blood pressure measurement at routine ANC visits, and Referred if blood pressure is high, or Referred if blood pressure is high outside of the routine ANC visit	Health worker clinical decision support Feedback dashboards with action items

^a^ANC: antenatal care.

^b^eRegistry: electronic registry.

**Table 3 table3:** Secondary outcomes, data sources and definitions.

Secondary outcome	Sources of data	Measurement sequence	Definition	Intervention subcomponents with assumed direct effect
Timely first ANC^a^ visit	Case records from the eRegistry^b^ Postpartum household survey	Registrations continuously at point of care Household visit after the completion of pregnancy	Proportion of women that have an ANC visit at or before 16 weeks among those with a home pregnancy registration before 16 weeks	Targeted Client Communication via SMS text message: ANC appointment reminders
High-risk women successfully referred to a skilled provider for additional care	Case records from the eRegistry Postpartum household survey	Registrations continuously at point of care Household visit after the completion of pregnancy	Proportion of women that received additional care during pregnancy among those that are referred for severe anemia, or hypertension or diabetes during pregnancy	Health worker clinical decision support Targeted client communication via SMS: Referral reminders, high risk, facility delivery reminders

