### Strengths and Limitations

An important strength of the trial lies in the design and implementation of the intervention. We continuously engaged both health workers and clients to develop tailored DHIs. The eRegistry supports the creation of a single, individual-level health record across multiple cadres of health workers; few other initiatives have made efforts to implement such a system designed to provide continuity of data and care. The trial outcomes are meant to capture different aspects of the intervention, allowing for better interpretations of the effect while serving as another strength of the study.

This study had some limitations. Reduced fidelity to the use of the eRegistry as the primary documentation tool will adversely affect the DHIs driven by the entered data. The eRegistry is not set up to provide automated monthly public health reports. Public health reports are still largely paper-based, with one cadre of health workers using the DHIS2 system separately for aggregate reporting purposes. This continued use of paper-based documentation and aggregate reporting may lead to incomplete data entry into the eRegistry, thus affecting the optimal delivery of DHIs. The eRegistry is used only in public sector health clinics at the primary care level. As a result, the results of the trial are only indicative of care provision and utilization in the public sector. The health system landscape in our study area also comprises private and NGO-run health care providers, and clients are known to seek antenatal care from multiple providers. We will report on clients’ utilization of antenatal and delivery care from all health care providers, with the data collected during the postpartum household visit.

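### Primary outcome 2 (hypertension screening and management) is scored only from eRegistry entries by unblinded staff, and the intervention acts on recording as well as care, so completeness may differ by arm

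*Protocol article*

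**What the plan says.** **Source of the outcome.** Table 2 (Outcomes) lists "Case records from the eRegistry" as the sole source for primary outcome 2, with the measurement sequence "Registrations continuously at point of care". The components named as acting on it are clinical decision support and "Feedback dashboards with action items".

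**What differs by arm.** Under Intervention Arm, "The decision support comprised referral and counseling reminders, medication alerts, and scheduling"; the dashboards carry hypertension screening and management indicators, and data entry triggers every digital intervention. Under Control Arm, users get only basic validation warnings, and "The eRegistry in the control arm was set up such that control users had no access to client records entered by other users".

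**What is the same.** The Intervention overview says that paper documentation continued in both arms throughout. Blinding says that facility-based workers could not be blinded.

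**What is acknowledged.** Strengths and Limitations says that continued paper documentation "may lead to incomplete data entry into the eRegistry, thus affecting the optimal delivery of DHIs". Adherence promises indicators of eRegistry use across intervention and control clusters. Neither section mentions the effect of incomplete entry on outcome measurement.

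**The concern.** The tool that delivers the intervention is also the tool that measures this outcome. A blood pressure reading or referral can be provided, noted on paper and never entered. In the intervention arm, entry brings a prompt and a visible score on the indicators that make up the outcome. In the control arm it brings neither. Even if care were identical, the intervention arm could show more recorded screening and referral.

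What is at stake is the meaning of a positive result. As planned, the analysis cannot separate better hypertension care from better recording of the same care.

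**Working it through.** **1. Sources across outcomes.** Tables 2 and 3 list seven outcomes. Timely antenatal attendance and severe postpartum anemia use the postpartum survey. Timely first visit, successful referral, facility delivery, and severe morbidity or mortality combine survey and eRegistry. Only hypertension screening and management has no survey source. Survey interviewers are independent project staff (Data Collection) blinded to allocation (Blinding); those who enter outcome 2 are not blinded.

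**2. The plan's power figure.** Inputs from Sample Size and Cluster Level: 12% against 22%, intracluster correlation 0.1, 29 control and 30 intervention clusters, cluster size 77 women (or 140 contacts). Two-sided alpha of 0.05 is assumed.

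- 77 per cluster: design effect 1 + 76 × 0.1 = 8.6; effective sizes 29 × 77 / 8.6 = 259.7 and 30 × 77 / 8.6 = 268.6; power 86.6%.
- 140 per cluster: design effect 1 + 139 × 0.1 = 14.9; effective sizes 272.5 and 281.9; power 88.2%.

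The stated power above 80% is reproduced. The point concerns measurement, not sample size.

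**3. Size of a recording effect.** Simple model: observed proportion = true proportion × completeness of recording. True care is set at 22% in both arms, so the true risk ratio is 1.0. The completeness values are assumptions.

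| Completeness, control / intervention | Observed, control | Observed, intervention | Risk ratio |
|---|---|---|---|
| 80% / 95% | 0.22 × 0.80 = 17.6% | 0.22 × 0.95 = 20.9% | 1.19 |
| 70% / 90% | 0.22 × 0.70 = 15.4% | 0.22 × 0.90 = 19.8% | 1.29 |

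**4. Chance of a false positive.** Fix the observed control proportion at 12%, assume no true difference, and let the intervention proportion be 12% times the completeness ratio. With the effective sizes in step 2, the probability of a significant result favouring the intervention is 2.5% at ratio 1.0, about 6% at 1.1, 17–18% at 1.25 and 49–51% at 1.5.

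**5. What a tipping-point analysis would show.** Under the same model, true risk ratio = observed risk ratio / completeness ratio, so significance is lost once the completeness ratio reaches the lower confidence limit. Suppose the trial observed exactly its target, 0.22 / 0.12 = 1.83. With 77 per cluster, SE(log RR) = √[0.88 / (259.7 × 0.12) + 0.78 / (268.6 × 0.22)] = √(0.0282 + 0.0132) = 0.204. The lower limit is exp(0.606 − 1.96 × 0.204) = 1.23 (1.24 with 140 per cluster). Completeness of 80% against 95% (ratio 1.19) would leave that result significant; 70% against 90% (ratio 1.29) would not.

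**The case against.** **Central extraction.** The control-arm access limit governs what a user sees on screen. A data manager extracts outcome data from the server (Data Management), biometric identification was available in both arms, and a typical facility has one permanent clinical cadre (Study Setting). A reader might infer that a control woman's entries split across users count as care not given. The article states no such scoring rule. This stands, and the argument rests on the sole source and the arm-specific prompts instead.

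**Direction.** Table 2 refers to women with at least one antenatal visit at a randomized facility. If that fixes the denominator, women whose visits were never entered may drop out and not count as failures. Fuller recording of high readings also creates more women who need a recorded referral, which could lower the intervention score. Imputation of missing data is to be considered. This stands: bias towards the intervention is likely, not established.

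**Mitigation.** Control staff also enter data digitally, training and support were similar, and adherence indicators will be reported. Dashboards began only in June 2019, while enrollment began in October 2018. These reduce the risk. They do not equalise the prompt or incentive to record, and descriptive indicators of use do not show whether readings and referrals are complete.

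**Source statements.** The Outcomes text names both sources for the outcomes as a whole, and Individual Level says outcome data came from the survey. Table 2 is the specific statement, and it gives this outcome the eRegistry alone.

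**Size.** A reader might infer that the whole target effect could be a recording artefact, since completeness of 0.12 / 0.22 = 55% against 100% reproduces it. That requires perfect intervention-arm entry despite parallel paper records, and the 12% comes from a Demographic and Health Survey, not from under-recorded eRegistry data. The article supports no such gap.

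**Conclusion.** The concern holds as a structural risk of differential ascertainment in one primary outcome. What the article establishes is a single data source, unblinded recorders, prompts and feedback in one arm only, and a paper route around the eRegistry in both. It does not report that completeness differed.

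The size is unknown. The risk ratios of 1.19 and 1.29 rest on assumed completeness, on true care of 22% in both arms, and on omissions counting as failures. Under that model, even a result equal to the target effect would lose significance at a completeness ratio of about 1.23, so modest differences matter.

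Table 1 is a separate point. In the facility section, the row "Digital client health records" has a mark only for the intervention arm, while the Intervention overview and Control Arm text say control workers used these records. A reader might infer that control facilities had no digital record to score. The text contradicts that, and Table 1 also repeats a block of rows, so a table error is plausible. The passages need reconciling, but the cell is not evidence of differential recording.

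This should be fixed. It calls for added analyses and careful wording, not a new primary definition.

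**What to change.** Keep the primary definition and specify the following before the actual allocations are used. The article says code is developed on dummy allocations, which leaves room for this.

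1. **Completeness by arm.** For women surveyed from June 2019, report by arm the share of survey-reported antenatal visits at randomized public facilities that appear in the eRegistry with a blood pressure entry, linked by study ID.
2. **Tipping point.** Re-estimate outcome 2 over a grid of differential recording completeness. State in advance that, if the result is not robust, the claim is limited to recorded screening and referral.
3. **Supportive survey version.** Where the questionnaire permits, derive blood pressure measured and referral reported. This should not gate the primary claim: the questionnaire is not shown, and the article mentions referral care seeking, which is not the same as a provider's referral.
4. **Scoring.** Pool all users' records for each woman before scoring, using only fields common to both arms.
5. **Table 1.** Reconcile the control cell with the text.

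The cost is mainly extra analysis of data already collected. The survey relies on recall, covers only a subset of pregnancies from June 2019, and draws its list from eRegistry registrations, so it can reveal unentered visits but not unregistered women.
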